### 2.9. Recruitment

Patient recruitment will take place in Aachen, Frechen (a small town near Aachen), and the surrounding areas. We expect that approximately 50% of all parents will be willing to participate in the study and will consent to the study assessments; thus, recruitment at the two sites will guarantee that the required sample size will be achieved within 24 months of recruitment. The drop-out rate until 1-year follow-up is estimated to be 20%, according to Suchman et al. (2013) [57]. Before the start of the study, the EPP in Aachen cared for an average of 249 parents per year (2016: 255; 2017: 231; S018: 260). However, due to the COVID-19 pandemic, recruiting difficulties have occurred, so recruitment proceeded much slower in some phases, to the point that a study design change became necessary (see also [8]). Participants are paid EUR 50 for each assessment session.

### 2.10. Plans for Assessment and Collection of Outcome Data

There are three measurement time points. All assessments will take place during home visits and be performed by the study staff (psychologists). All psychometric questionnaires will be completed on mobile devices, and the answers will be recorded with LimeSurvey software (Version 3.28.58). Clinical interviews will be carried out by a study employee who is trained in the procedures. In addition to the outcomes, sociodemographic data (such as partnership status and housing situation) and the socioeconomic status of the family will be collected according to the GEDA study by the Robert Koch Institute [58] and via a case report form (CRF). An overview of the diagnostic tools and when data will be collected can be found in Table 2.

### 2.11. Ethical Approval

The trial was approved by the local Research Ethics Committee at the University Hospital RWTH Aachen (reference EK 221/19) and will be carried out in accordance with the Declaration of Helsinki. The study was registered at the German Clinical Trials Register (DRKS00022075 on the 8 July 2020). Written, informed consent to participate will be obtained from all participants, both parents and EPP staff.

### 2.12. Statistical Methods for Primary and Secondary Outcomes

The effects of the “EPP-plus” are assessed in a pre-post comparison using the PSI scores with a one-sample t-test with a two-sided significance level of 5%. The primary analysis is based on the intention-to-treat (ITT) principle, which aims to include all subjects enrolled in the feasibility study. The analysis of the secondary results is carried out analogously. Exploratory analyses will investigate which family-level risk factors are associated with the magnitude of change in PSI, using linear models and considering the presence of socioeconomic disadvantage (e.g., unemployment, overall socioeconomic status), mental risk characteristics (e.g., mental/physical health, domestic violence), teenage motherhood, immigrant status, parental ELM (assessed by CECA-Q), AAPI-2 pre-intervention total score, age and gender (of parent and child), and child responsiveness (Infant Care Index).

The feasibility of the “EPP-plus” approach will be analyzed descriptively, using frequencies and proportions for nominal or ordinal variables or medians and interquartile ranges for quantitative variables. For feasibility, we will consider the median number of visits per family, the number of supervision sessions, and attendance by the EPP staff to supervision sessions. In addition, acceptance of the “EPP-plus” approach by the staff members and their work-related stress levels will be analyzed at the start, midterm, and end of the trial by linear mixed models accounting for the clustering of team members. Furthermore, potential staff- and team-related factors contributing to the outcome of the “EPP-plus” approach (such as job experience, professional background, etc.) will be analyzed.

All safety data, including adverse events, are analyzed descriptively in the Safety Population (SP), which includes all families who were visited at least once by a team member of the “EPP-plus” team.

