## 1. Introduction

Many different risk factors for the occurrence of maltreatment in burdened families have been identified. Most of these risk factors have been found at the parental level [1]. For instance, low parental education and low family income levels have been shown to be risk factors for child abuse and neglect [2]. Additionally, parents with their own experiences of early life maltreatment (ELM) are more likely to maltreat their children, potentially leading to an intergenerational cycle of abuse and neglect [3,4,5]. Thereby, various pathways may explain the transmission, including learning theory, disorganized attachment, epigenetic aspects, and intergenerational transmission of psychopathology [6]. A recent cross-sectional study underpinned these previous findings by examining the transmission across three generations, grandparents, parents, and young adults, and found continuity for maltreatment across all three generations [7]. A meta-analysis of 84 studies provided a qualitative summary of the current knowledge regarding this cycle. These results indicated that the risk of child maltreatment in families in which the parents experienced ELM was almost three times higher than that in families in which the parents did not experience ELM [6]. There is also evidence that socially isolated parents may be more prone to maltreating their children [8]. Parenting stress, in general, is another identified risk factor for child abuse and neglect. Crum and colleagues conducted a study to assess the relationships between parental stress, abuse potential, and social and behavioral outcomes in children. The results demonstrated that parental stress was consistently linked to abuse potential, supporting the association already determined in previous research [9]. Parents with mental illness are also at an increased risk of maltreating their children [10]. In a recent study, persistent maternal depressive symptoms mediated the relationship between maternal history of maltreatment and current parenting stress at the 18-month assessment during a home-visiting prevention program [11]. Mothers with depression were much more likely to have a child for whom maltreatment was reported than mothers without depression [12]. Other psychiatric disorders, such as borderline personality disorder [13] or substance abuse, are also associated with an increased risk of parental ELM and child abuse. Overall, parents with a high psychosocial and economic burden are at risk of maltreating their children and prematurely dropping out of support programs that aim to prevent child abuse and neglect [14]. Early dropout represents a particular challenge for such programs. Special attention must be paid to these hard-to-reach clients to ensure effective support.

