### 2.8. Sample Size

In the current study, we will analyze whether there is a statistically significant change in the primary outcome (PSI score for each parent) from T0 (preintervention) to T2 (follow-up assessment, paired comparison). With a sample size of 67 parents (with data at both time points), a power of 80% can be achieved (two-sided significance level of 0.05; one-sample t-test) for an effect of at least d = 0.35 (standardized difference in the mean; calculated with G * Power 3.1.9.6). Effects of this magnitude were observed for an MBT team approach in mothers (Suchman et al., 2013, moderate effects on caregiving behavior and child behaviors (d > 0.2), [57]) and are therefore also expected for the new “EPP-plus” approach. Taking into account a loss to follow-up rate of up to 20% (missing values in the primary outcome measure at FU), at least 84 study participants should be recruited.

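### The primary analysis is labelled intention-to-treat for all enrolled families, but the stated t-test can use only those with both T0 and T2 PSI, planned as 67 of 84

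*Protocol article*

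**What the plan says.** Section 2.12 describes the primary analysis as a "pre-post comparison using the PSI scores with a one-sample t-test with a two-sided significance level of 5" per cent. The next sentence gives the population: "The primary analysis is based on the intention-to-treat (ITT) principle, which aims to include all subjects enrolled in the feasibility study". Secondary outcomes are to be analysed in the same way.

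Section 2.8 defines the contrast as the change "from T0 (preintervention) to T2 (follow-up assessment, paired comparison") and states: "With a sample size of 67 parents (with data at both time points), a power of 80% can be achieved". The target effect is given as "for an effect of at least d = 0.35 (standardized difference in the mean; calculated with G * Power 3.1.9.6"). The step to 84 recruits is introduced with "Taking into account a loss to follow-up rate of up to 20% (missing values in the primary outcome measure at FU").

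Table 2 schedules PSI at T0, T1 and T2. Section 2.12 names linear mixed models for the staff outcomes only.

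On dropout, the Introduction says that parents with a high psychosocial and economic burden are at risk of "prematurely dropping out of support programs that aim to prevent child abuse and neglect". Section 2.2 makes better retention of hard-to-reach parents in the care programme one of the study's aims.

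**The concern.** The named test, its planned n and its population label do not fit together. A one-sample t-test on T0-T2 change needs both values from each family, so as written it is a complete-case analysis. Recruiting 84 instead of 67 protects power. It does not bring the lost families into the estimate.

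This would matter little if families were lost at random. The trial, however, recruits burdened families and treats keeping them engaged as something the intervention should change, so random loss cannot be taken for granted. With a single arm there is no comparison group in which similar losses could offset the bias, and any selection goes straight into the estimated change. Section 2.2 presents this study as the first step before a large cluster-randomised trial, so a distorted effect size could be carried into that design.

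**Working it through.** **1. The plan's own figures.** Inputs from Section 2.8: d = 0.35, two-sided alpha 0.05, power 80%, one-sample t-test, 20% loss.

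- Power is the probability that a noncentral t with n - 1 degrees of freedom and noncentrality d√n exceeds the two-sided 5% critical value.
- At n = 67 the noncentrality is 0.35 × √67 = 2.86 and power is 0.806. At n = 66 power is 0.7999. The smallest adequate n is 67, as stated.
- 67 / (1 - 0.20) = 83.75, rounded up to 84, as stated.

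The sample size is correct.

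**2. Who is in the test.** 84 - 67 = 17 families, and 17/84 = 20.2% of the declared intention-to-treat set contributes nothing to it.

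**3. Completer effect against all-enrolled effect.** The article gives no figure for change in families lost, so this is an assumption. Let completers improve by 0.35 SD of change and let the lost 20% improve by m on average. The all-enrolled mean is 0.8 × 0.35 + 0.2 × m.

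| m in lost families | All-enrolled mean | Completer mean minus all-enrolled |
|---|---|---|
| +0.35 | 0.350 | 0 |
| +0.175 | 0.315 | 0.035 |
| 0 | 0.280 | 0.070 |
| -0.175 | 0.245 | 0.105 |
| -0.35 | 0.210 | 0.140 |

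If m were above 0.35, the completer mean would understate the all-enrolled effect.

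**4. Bias by dropout mechanism (simulation).** All settings are assumptions: 84 families, no true change, 20% missing at T2, PSI correlations of 0.6 (T0-T1), 0.6 (T0-T2) and 0.7 (T1-T2), and logistic dropout with log-odds 1 to 2 per SD of the driving variable. Bias is in SDs of PSI, and a negative value is a spurious fall in stress.

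| Loss at T2 depends on | Completer bias | t-test behaviour |
|---|---|---|
| Rise from T0 to T1 | -0.09 to -0.15 | rejects in 14% to 28% of trials (nominal 5%) |
| High T0 burden | +0.07 to +0.10 | false favourable result in 0.6% to 0.2% (nominal 2.5%) |
| T1 level | -0.02 to -0.03 | rejects in 5.3% to 5.6% |

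To compare with d = 0.35, which is in SDs of change, divide by √(1 + 1 - 2 × 0.6) = √0.8 = 0.894. The first row becomes -0.10 to -0.17 and the second +0.08 to +0.11. The second row is unfavourable because of regression to the mean: families with high T0 scores tend to fall most, and these are the ones lost.

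**5. Likelihood estimate from T0, T1 and T2 in the same simulations.** When T1 is observed in the lost families, bias is about zero under all three mechanisms. The standard error is similar to the completer test's (about 0.106 to 0.107 against 0.103 to 0.111). If families lost at T2 also lack T1 and loss follows the T0-T1 rise, a bias of -0.07 to -0.10 remains, about 70% of the completer bias.

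**The case against.** **The missing-data method may be in a document not shown.** This is a condensed article, the wording says only that the analysis aims to include everyone, and a t-test after multiple imputation would be compatible with both sentences of Section 2.12. This stands in part. The absence of a missing-data method is not the point here. The point is that the article itself names a two-value test, plans its n on families with both values and calls it intention-to-treat. The inflation in Section 2.8 does not rule out imputation, but nothing in the article points to it.

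**A reader might infer that the bias must favour the intervention, because the most burdened parents leave early.** The article does not support this. The Introduction concerns parents leaving support programmes, not missing the T2 assessment. T2 is timed by the child's age (Section 2.7), done by study psychologists at home (Section 2.10) and paid at EUR 50, so a family that has left the programme can still give T2 data. Burden at entry is also the mechanism closest to that text, and in the simulation it biases the completer mean in the unfavourable direction. For the same reason the 69% who stayed in care for less than three months before the study is not a missing-data rate.

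**The remedy is not perfect.** This stands. The model relies on missingness depending on observed PSI. It protects less where T1 is missing too, and T1 falls at a different time for each family.

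**This is a feasibility study.** The Discussion leaves effectiveness to later randomised trials. This also stands, and it lowers the severity.

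**Conclusion.** The point holds as a mismatch between label and test. The stated primary analysis leaves out about 20% of the population it claims and does not use the T1 PSI. That follows from Sections 2.8 and 2.12 alone, without any assumption about who is lost. Section 2.8 is what fixes T2 as the endpoint; Section 2.12 says only pre-post, and the same gap would arise for a T0-T1 change.

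The consequence for the estimate is conditional. Under the assumed correlations, 20% loss and dropout log-odds of 1 to 2, the completer bias runs from about -0.15 to +0.10 PSI SD depending on the mechanism, and false rejection reaches 14% to 28% only if loss follows worsening from T0 to T1. A claim that the t-test will overstate benefit, or that the protocol reports selective loss at T2, would go beyond the text. The sample size needs no correction. Severity: should be fixed before analysis.

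**What to change.** Make the primary analysis a likelihood-based repeated-measures model of PSI at T0, T1 and T2 with unstructured covariance, in all enrolled families with a T0 PSI and with T2 minus T0 as the contrast. Name that contrast in Section 2.12. Keep the one-sample t-test as a sensitivity analysis and label it complete-case. Add a delta-shift analysis for families lost to T2, including the case of no improvement, because the model cannot address loss that depends on unobserved stress. Report how many families lost at T2 have a T1 PSI, since the model's advantage depends on it. Apply the same approach to secondary outcomes measured at T0 and at a later visit.

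If the t-test is kept as primary, the minimum is to call it complete-case, or to state that missing T2 values are imputed before the test.

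The cost is a little more analysis work. All three PSI assessments are already scheduled, and no extra data or families are needed. The remaining weaknesses are the assumption about missingness, the weaker protection where T1 is also missing, and the varying timing of T1.

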### 2.2. Study Design

The current trial is a single-center, non-randomized, open-label, single-arm feasibility study, including two local EPP teams in the wider area of Aachen, Germany. It is part of a larger consortium (the UBICA-II study), including an MBT-based intervention trial for psychiatric patients who are parents [34]. A total of at least 84 families in the care of the EPP will be systematically assessed at three time points: at the beginning of support from the welfare system (preintervention; T0), when support ends (postintervention; T1), and when the child is 12, 18, 24, or 30 months old, depending on their age at the time of inclusion in the study (follow-up; T2). The trial was approved by the local Research Ethics Committee at the University Hospital RWTH Aachen (reference EK 221/19) and will be carried out in accordance with the Declaration of Helsinki. The study was registered at the German Clinical Trials Register (DRKS00022075 on 8 July 2020). The study protocol was adapted in 2020, when it turned out that, due to the COVID-19 pandemic, the originally planned non-randomized study design with the nonconcurrent recruitment of two groups (first, a control group receiving usual EPP support, followed by the training and subsequent recruitment of the EPP employees for the “EPP-plus” intervention (experimental condition)) would not lead to comparable group conditions. Thus, the study was modified to a non-randomized, single-arm feasibility study. The aims of the feasibility study were adapted and now include evaluating (1) the acceptance of the approach by the EPP staff, (2) the burden of the EPP staff, and (3) the success of the EPP staff to better retain hard-to-reach parents/caregivers in the care program, in addition to our measures for the risk of maltreatment by parents. We chose a non-randomized, single-group feasibility study design for the following reasons: the EPP support systems vary across Germany with respect to type, dose, and mode of interventions, professional backgrounds, frequency of supervision and networking of the team, and legal and financial situations. Thus, it is not possible to choose a (non-randomized) comparable concurrent control group from another geographical region. Due to the planned team intervention, the randomization of individual staff members or individual parent dyads would have been impossible. The possible alternative approach of a cluster-randomized controlled trial with randomized teams would have resulted in very large sample sizes, e.g., for an effect size of d = 0.4, we would need 26 clusters with approximately 30 families each (total of 780 families) or approximately 23 clusters with 50 families each (total 1180 families), with an expected intracluster correlation coefficient of 0.1, entailing huge costs and logistical efforts. Since neither the feasibility nor estimated effect sizes on parents have been investigated for this mentalization-based team approach before, our current study is a necessary first step before such a large cluster-randomized trial.

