
### 2.3. Study Setting

The trial is being performed at the Department of Child and Adolescent Psychiatry, Psychotherapy and Psychosomatics, University Hospital RWTH Aachen. Data collection takes place via home visits. The EPP teams from Aachen and Frechen, a small town near Aachen, are participating in the study. Both sites are located in Germany. The study is part of the UBICA-II consortium with researchers from Berlin and Heidelberg (see https://www.ubica.site/tp_fruehehilfen.html (accessed on 2 January 2024) for more information). The Coordination Centre for Clinical Trials (KKS) in Heidelberg monitors the data, and the Institute of Medical Informatics and Statistics (IMIS) in Kiel is responsible for statistical planning and analysis.

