### 2.4. Eligibility Criteria

We identified two EPP teams in Aachen and the surrounding areas with comparable team structures and professional backgrounds (i.e., family midwives, social workers, or pediatric nurses). These teams are typical of EPP teams in either rural or urban German regions. The majority of staff members in the teams have to provide informed consent to participate in the trial. We consecutively include all families (mothers or fathers and their children) seeking support in the EPP. The inclusion and exclusion criteria are summarized in Table 1. The risk factors were previously identified according to a large sample of 837 at-risk families [33]. Parents of children aged ≤ 24 months or women in the third trimester of pregnancy will be included at the start of the intervention. Participants must provide informed consent for data collection within the trial. No other exclusion criteria will be used to achieve maximum generalizability and representativeness. In families with insufficient knowledge of German, data collection will be carried out with the help of a translator. Support by the EPP is available for families who are not participating in the study. However, the intervention of the EPP corresponds to the “EPP-plus” approach for nonparticipating families as well since the entire team has been trained in the MB-TA. Thus, inclusion in the study only means that additional data will be collected from parents, not that a different intervention will be provided.

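### The exploratory PSI-change models carry no team term, so a family factor that is unevenly spread over Aachen and Frechen could take up part of any team difference

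*Protocol article*

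**What the plan says.** Section 2.12 describes the family-level work as follows: "Exploratory analyses will investigate which family-level risk factors are associated with the magnitude of change in PSI, using linear models". The named factors are socioeconomic disadvantage, mental risk characteristics, teenage motherhood, immigrant status and parental early life maltreatment (ELM), and the list closes with "AAPI-2 pre-intervention total score, age and gender (of parent and child), and child responsiveness (Infant Care Index". Team and site do not appear.

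The team level does appear elsewhere in section 2.12. Staff acceptance and stress are analysed "by linear mixed models accounting for the clustering of team members". A further sentence says that "potential staff- and team-related factors contributing to the outcome of the “EPP-plus” approach (such as job experience, professional background, etc.) will be analyzed"; it names no model and does not mention the family-factor coefficients.

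On the setting, section 2.2 describes the trial as "including two local EPP teams in the wider area of Aachen, Germany", and section 2.3 says: "The EPP teams from Aachen and Frechen, a small town near Aachen, are participating in the study". Section 2.4 says the teams were chosen for comparable structure and professional background, and adds: "These teams are typical of EPP teams in either rural or urban German regions". Section 2.2 also sizes a rejected alternative, a cluster-randomised trial, "with an expected intracluster correlation coefficient of 0.1".

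**The concern.** With one city team and one small-town team, a factor such as immigrant status or socioeconomic disadvantage could plausibly be more frequent in one caseload. If the teams also differ in average PSI change, a model without a team term compares families partly across teams. The factor's coefficient then mixes its own association with the difference between teams.

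These models serve stated aims. The second aim in the Introduction is the association between parental risk factors, including ELM, and the effectiveness of care. Section 2.1 makes the modulating role of ELM the secondary objective. A factor that looks linked to PSI change only because it is commoner in one team's area would mislead on which families benefit.

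**Working it through.** **Inputs from the protocol.** 67 parents with data at both time points, two-sided 5% level, d = 0.35, 20% loss to follow-up (section 2.8); two teams and an ICC of 0.1 (section 2.2).

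**The plan's own figures.** A one-sample t-test with n = 67 and d = 0.35 has power 0.806, and 67 / 0.8 = 83.75, rounded up to 84. Both stated sizes reproduce. The cluster-trial figures follow from about 100 families per arm and a design effect of 1 + (m − 1) × 0.1:
- m = 30: 200 × 3.9 = 780 families, or 26 clusters.
- m = 50: 200 × 5.9 = 1180 families, or 23.6 clusters.

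So the 0.1 is an input to that hypothetical trial.

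**Assumptions, not in the documents.** The ICC applies to PSI change; each team's share of the 67 families; the prevalence of a binary factor in each team; the factor has no true effect; each factor is tested at 5%.

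**Size of the team difference.** Two teams drawn at random differ with standard deviation √(2 × ICC). At ICC 0.1 this is √0.2 = 0.45 outcome SD, with a mean absolute difference of 0.36 SD.

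**Share passed to the factor.** Bias = team difference × [P(team A | factor) − P(team A | no factor)]. With equal teams:
- 40% and 40%: the bracket is 0, so there is no bias.
- 50% and 20%: 0.5/0.7 − 0.5/1.3 = 0.714 − 0.385 = 0.330; bias SD 0.330 × 0.447 = 0.15.
- 60% and 20%: 0.6/0.8 − 0.4/1.2 = 0.750 − 0.333 = 0.417; bias SD 0.417 × 0.447 = 0.19.

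**From bias to false positives (60% and 20%, equal teams, ICC 0.1).**
- Overall prevalence is 0.40, so n·p·q = 67 × 0.24 = 16.08.
- Sampling SE is √(0.9/16.08) = 0.237. With the bias SD of 0.186, the actual spread is √(0.0560 + 0.0347) = 0.301.
- The squared correlation of team and factor is 0.4² × 0.25 / 0.24 = 0.167. The residual variance seen by the model is 0.9 + 0.2 × 0.25 × (1 − 0.167) = 0.942, so its SE is √(0.942/16.08) = 0.242.
- The ratio is 0.301/0.242 = 1.24. The two-sided tail beyond 1.997/1.24 = 1.61 is about 11%.

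**Simulation.** Linear model without a team term, n = 67, ICC 0.1, 4,000 to 6,000 runs per scenario; the higher prevalence is in the larger team. Where two sets of runs exist, both ends are shown.

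| Prevalence | Teams 34/33 | Teams 50/17 |
|---|---|---|
| 40% / 40% | 5.0% | 5.4% |
| 50% / 30% | 6.7% | 6.3% |
| 50% / 20% | 8.2% | 7.1% |
| 60% / 20% | 11.0% to 12.3% | 7.5% to 8.8% |

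A more extreme contrast of 70% against 20% gives 15% and 11%. At ICC 0.05 the unadjusted rate is 5.1% to 7.9%. At ICC 0.02 it is 5.4% to 6.4% for contrasts from 40%/20% to 60%/20%. With team in the model the rate is 4.5% to 5.6% in all scenarios where it was run, and the coefficient is centred on zero.

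**The case against.** Four points on the other side carry weight.

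- A reader might infer that the protocol itself expects these two teams to differ. It does not say so. The ICC belongs to a hypothetical trial of about 23 to 26 teams and is not tied to PSI change, and section 2.4 calls the two teams comparable. This stands, although that comparability concerns structure and professions, not the families served.
- A reader might infer that Aachen and Frechen families differ in the listed factors. No section reports this, and the sentence on rural and urban regions describes what the teams are typical of, not their caseloads. This stands, so the mechanism is conditional.
- A reader might infer that the plan ignores the team. It does not: staff- and team-related influences on the outcome are to be analysed. But a separate analysis of traits such as job experience does not adjust the family-factor coefficients, so the point is not cured.
- Site as an adjustment term in an exploratory model is often left to the analysis plan, and the listed factors can be read as candidates, not as a closed model. This lowers the priority. It does not remove the point, because the article names its variables in some detail and all are at family level.

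The models are also labelled exploratory, with no significance threshold of their own, and nothing in the documents suggests that ELM would differ by site.

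**Conclusion.** The point holds in a limited, conditional form. The named variables leave out team, and nothing else in section 2.12 adjusts the family-factor estimates for it. Harm arises only if a factor is unevenly distributed over the two sites and the teams differ in PSI change; even then the factor takes up only part of the team difference.

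Under assumed ICCs of 0.02 to 0.1, 67 families and contrasts up to 60% against 20%, the false-positive rate for a null factor runs from about 5% to about 12%, against about 5% with a team term. The upper end needs the highest ICC, the widest of these contrasts and equal team sizes together; with a 50/17 split it stays below 9%. The documents give neither the prevalences nor the split. A stronger reading, that the trial's main result is compromised, has no support: the primary t-test and the sample size do not depend on these models. This is a worthwhile refinement of optional priority.

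**What to change.** In section 2.12 or the analysis plan, state that every exploratory model of PSI change, including the one for ELM, contains team (Aachen or Frechen) as a fixed effect, so that factor coefficients are within-team comparisons. Two teams are too few for a random effect. The term is there for adjustment and should not be read as a test of what makes one team more effective.

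The cost is one degree of freedom and a line of wording. Team should be known for every family, so no new data are needed.
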